### Intervention

After inclusion in the trial, baseline assessments will be performed, and hereafter patients will be randomized (1:1) to one of two arms receiving either (1) physiotherapy with nutritional supplementation and anabolic steroid (INT) or (2) physiotherapy with nutritional supplementation and placebo (CON). See Fig. 1 for a flowchart of the trial.

**Fig. 1 Fig1:**
[figure not shown]
Flowchart of enrollment, randomization, and trial-related activities

#### Trial medication

Nandrolone is a synthetic anabolic-androgenic steroid; it is protein-building, promotes mineralization of bones, and stimulates the formation of red blood cells. Nandrolone is structurally related to naturally occurring testosterone, but it shows enhanced anabolic effect and a reduced androgenic effect. Nandrolone is used medically in the form of esters (nandrolone decanoate) and is intended for use in osteoporosis in postmenopausal women and for some types of anemia. Deca-Durabolin is an intramuscularly administered depot preparation of nandrolone decanoate.
*Active arm (INT)*: Patients will receive intramuscular injections of nandrolone decanoate (Deca-Durabolin 50 mg/ml; Aspen, Durban, South Africa) every 3 weeks. The first injection will be administered at baseline and the last injection at week 12. The solution is injected into the gluteal muscle or rectus femoris. The dosage varies, dependent on gender and testosterone level (men). Women will receive 50 mg, men with total testosterone ≥ 11 nmol/L will receive 100 mg, and men with total testosterone < 11 nmol/L will receive a dose of 200 mg. The cut of 11 nmol/L for total testosterone is determined on the basis of the age-related reference interval (men 50–70 years, 8.4–25.4 nmol/L) and lies below the mean value of 14.6 nmol/L (24).*Placebo arm (CON)*: Patients will receive a placebo injection of 1 ml of sodium chloride 9 mg/ml (produced by Fresenius Kabi, Bad Homburg, Germany), following the same intervals as for the active agent. The fluid is injected intramuscularly, and the product has no therapeutic effect.

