#### General trial treatment procedures

Patients included in the trial will be treated according to the department’s standard procedures for surgery, anesthesia, and perioperative care. Type of operation is determined by a well-defined algorithm based on the type of fracture [32]. Standard perioperative care includes D vitamin and calcium supplementation dependent on the patient’s individual level. Further, a standardized liberal transfusion protocol is used with transfusion if hemoglobin (Hb) is < 9.7 g/dl.

After enrollment, patients will be assessed in regard to the study’s primary and secondary outcomes. Thereafter patients are randomized, and the first injection of the trial solution is administered by the dedicated nurse. In case of the primary nurse being absent, a second nurse trained in the protocol will substitute for her.

After discharge, the patient will receive weekly telephone calls from the project coordinator in order to ensure and monitor compliance. The patient will be asked about the amount of consumed nutritional supplement and attendance at physiotherapy sessions. Further, the patient will be asked about their well-being in order to detect potential side effects of the intervention. An interview guide will be used to assure systematic collection of information.

Every 3 weeks, the patient will attend a control visit at the hospital. The dedicated nurse will carry out blood tests and inject the treatment solution according to randomization group. Compliance with the trial as well as outcome/safety parameters will be monitored. Further, the nutritional supplement covering the following 3 weeks will be handed out at the visit.

The intervention period for the nutritional supplementation and exercise intervention is 12 weeks. The patient will receive the last injection at week 12. Further, at the 12-week appointment, an activity monitor will be applied to the patient’s thigh (activPAL; PAL Technologies, Glasgow, UK), which will monitor activity the following week.

Follow-up will occur during week 14, when patients will be assessed according to the primary and secondary outcomes. To ensure that all potential side effects are detected, one last telephone call is conducted during week 16, and thereafter the patient will have no further obligations in relation to the trial. See Fig. 1 for the flow of enrollment and trial-related events.

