### Blinding procedure

The patients, healthcare providers, intervention deliverers, data collectors, and outcome assessors are all blinded to whether the patient has received trial medication or placebo. The only person not blinded is the nurse drawing the envelope and injecting the medication/placebo, but she has no other involvement in the trial. The nurse is instructed not to reveal to the patients to which intervention they are allocated. No effort will be made to blind the research hypotheses from the participants.

Blinding for the individual patient will be broken only in cases where the continued treatment of the patient requires knowledge of allocation. Twenty-four-hour access to unblinding is assured. If the code is broken, date and reason will be registered, and the envelope will be signed by the investigator.

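### The placebo is fixed at 1 ml, but the stated doses come to 2 ml or 4 ml in men, so in men injection volume is enough to identify the arm and puts patient blinding at risk

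*Protocol article*

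**What the plan says.** The Trial medication section of the protocol article gives one strength for the active product, "Deca-Durabolin 50 mg/ml", and three dose levels. "Women will receive 50 mg"; men with total testosterone of at least 11 nmol/L are assigned 100 mg; men below that cut-off "will receive a dose of 200 mg". Injections run every 3 weeks from baseline to week 12.

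For the placebo arm the same section says: "Patients will receive a placebo injection of 1 ml of sodium chloride 9 mg/ml". No variation by sex or testosterone is given. The one feature said to match the active arm is the timing of the injections.

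The Blinding procedure section then declares: "The patients, healthcare providers, intervention deliverers, data collectors, and outcome assessors are all blinded to whether the patient has received trial medication or placebo". The injecting nurse is the sole exception. For patients, the safeguard stated there is an instruction to her not to disclose the allocation. The section adds that the research hypotheses are not hidden from participants.

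**The concern.** A placebo protects the blind only if it cannot be told from the active treatment. Here a stated placebo volume and stated active doses conflict with a stated property of the trial. The issue is therefore not a detail that the article left to the full protocol.

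The outcomes are of a kind that patient blinding is meant to protect. The primary outcome is maximal voluntary knee-extension torque, tested with verbal encouragement (Primary outcome). It follows training in which patients do as many repetitions as they can in each set (Physiotherapy). Many secondary outcomes, and the weekly questions about well-being and side effects, are interviews. A man who has worked out his arm could try harder or less hard, or report differently. The pilot's estimates are to feed the sample size of a confirmatory trial (Discussion), so a distortion would carry forward.

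**Working it through.** **Inputs** (all from Trial medication): strength 50 mg/ml; doses 50 mg, 100 mg and 200 mg; placebo 1 ml. This assumes that every dose is drawn from the one strength stated.

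**Formula:** volume = dose ÷ strength.

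The women's dose reproduces the placebo figure: 50 ÷ 50 = 1 ml. The same formula for the other dose levels gives:

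| Category | Active dose | Active volume | Placebo volume | Ratio |
|---|---|---|---|---|
| Women | 50 mg | 50 ÷ 50 = 1 ml | 1 ml | 1 |
| Men, testosterone ≥ 11 nmol/L | 100 mg | 100 ÷ 50 = 2 ml | 1 ml | 2 |
| Men, testosterone < 11 nmol/L | 200 mg | 200 ÷ 50 = 4 ml | 1 ml | 4 |

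**Separation in men.** No man on active treatment receives 1 ml, and no man on placebo receives 2 ml or 4 ml. The two sets of volumes do not overlap, so volume classifies every man correctly. His testosterone category need not be known: 1 ml means placebo and anything larger means active.

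**Number of exposures.** Baseline and weeks 3, 6, 9 and 12 make five injections at most. Some men will have fewer, because Table 1 allows exclusion on PSA at week 3 and Criteria for discontinuation allows treatment to stop.

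**Number of patients.** Men are planned for, since sex is a stratification factor (Randomization and allocation), but their expected share is not given. Taking 20–40% as an assumption: 48 × 0.20 = 9.6 and 48 × 0.40 = 19.2, so about 10 to 19 of 48.

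**Effect on the estimate.** With allocation balanced within sex, a bias *b* in the men's between-arm difference shifts the overall difference by (share of men) × *b*, which is 0.2*b* to 0.4*b* under the same assumption. The documents give nothing from which to set *b*, so the calculation stops there.

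**The case against.** The strongest reply is that a volume sufficient to identify the arm does not by itself unblind anyone. A blinded person must see or feel the volume and know that men's active doses exceed 1 ml. Gluteal injection is allowed, which is out of the patient's view. The article does not say that patients are told the volumes. The nurse who handles the syringe is unblinded by design, and she keeps the envelopes in an office away from the hip fracture unit and the physiotherapy department. All of this stands, and it limits the point to a risk. It does not remove the mismatch, and a declared blind should not depend on patients failing to notice a two- or fourfold difference.

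A second reply is that masked syringes would be described in the full protocol. That is fair as to masking, and the article's silence on it is not the fault. The 1 ml, however, is stated. If volumes are in fact matched, the Trial medication section is wrong as printed.

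A reader might also infer several stronger things that the documents do not support:

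- *Assessors or physiotherapists are unblinded.* Nothing places them at the injection. The coordinator who makes the weekly calls is also the main assessor, so a patient's remark could reach that person, but this is only a possible route.
- *The oil-based active solution gives itself away against saline.* Table 1 lists arachis oil as an ingredient. That difference would apply to women as well, and it matters only if the fluid is seen. It cannot be used to argue a problem confined to men.
- *The nurse's role breaks the blind.* The Blinding procedure section says of her "but she has no other involvement in the trial", whereas General trial treatment procedures says "The dedicated nurse will carry out blood tests and inject the treatment solution according to randomization group". The first statement is loosely worded. Drawing blood is not outcome assessment, though, and no passage has her rating hirsutism, hoarseness or edema.
- *A false sex or dose effect will be reported.* The Statistical analyses section describes no analysis by sex or dose.

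**Conclusion.** The Trial medication section is wrong as written for a trial that declares its patients blinded. The placebo matches the active injection in women only. In men the implied active volume is two or four times the placebo volume, with no overlap, at up to five injections. This rests on the stated strength applying to all doses. About 10 to 19 patients are concerned if men make up 20–40% of the sample, which is an assumption.

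The conclusion is that patient blinding in men is at risk. It is not that every man is unblinded, nor that the primary result is biased by a known amount. No figure in the documents supports a numerical bias.

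This should be fixed, but it does not invalidate the pilot. The Sample size section says the trial explores an effect and does not establish one. The Discussion says the decision to proceed will not rest on a statistically significant difference, although the test results will be considered.

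**What to change.** Reconcile the Trial medication and Blinding procedure sections so that, within each sex and testosterone category, active and placebo injections cannot be told apart by volume or appearance. A matched placebo volume, a masked syringe prepared out of the patient's sight, or both would achieve this. The active doses and the injected volume that is acceptable are for the sponsor's clinicians and are not questioned here. If volumes are already matched in practice, correcting the printed 1 ml is enough.

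Flag the men already treated under the 1 ml placebo. If the mismatch was real, qualify the blinding claim for men in the trial report.

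The cost is a short amendment, some saline and syringe covers, and possibly a larger saline injection for men on placebo. Recruitment was planned to run to September 2020 (Trial status), so the change would protect later patients. It cannot restore the blind for those already treated.

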#### Nutritional supplementation

Patients in both arms will receive two daily nutritional drinks while under hospital admission, which is already a standard procedure at the unit. At discharge, patients will receive nutritional drinks covering the following 3 weeks. At every control visit at the hospital, additional drinks will be provided covering the next 3 weeks.

The protein-rich nutritional supplement is planned to account for at least 35% of the patient’s daily protein requirement. The recommendations for geriatric patients with acute disease is 1.2–1.5 g/kg body weight/day [31]. The standard used at the hip fracture unit is 1.35 g/kg body weight/day; this value will be used to calculate the protein supplementation throughout the study. The protein-rich nutritional supplement is a liquid containing 18 g of milk-based protein per bottle (RESOURCE 2.0 + fiber; Nestlé Health Science, Sydney, Australia). On the basis of the standard used in this study, dependent on their body weight, most patients will receive two bottles per day for 12 weeks.

#### Physiotherapy

Patients will receive physiotherapy as part of the department’s standard procedure, starting on the day after surgery and continued daily until day 3 postoperatively, and thereafter continued on weekdays. The standard physiotherapy treatment includes functional exercises, such as transfers and walking, and exercise therapy primarily aimed at lower extremities. An exercise guideline with 12 specific exercises focusing on joint movement, lower limb muscle activation, and edema prophylaxis will be handed out and progressed individually [3]. After baseline testing and randomization, knee-extension strength training using weight cuffs will be added. The intervention is adjusted to meet the abilities of the individual patient, considering their medical and prefracture status. On days of baseline testing, the testing replaces the normal physiotherapy intervention.

After discharge, patients will receive physiotherapy in the municipality, which is already a standard procedure in Denmark following a hip fracture. The patients will receive physiotherapy 1 h twice weekly up to and including the 12th week after inclusion in the study. The physiotherapy intervention in the municipality will typically be a group intervention, and it will be based on the patient’s individual level. The training will consist of a warmup (aerobic exercises such as cycling), functional training (e.g., walking exercises, climbing stairs, sit-to-stand exercise), balance training (with different degrees of support and different types of underlay), and lower limb exercises (e.g., using elastic bands and progressive strength training). In regard to strength training, two exercises will be obligatory (knee extension performed as unilateral and bilateral leg press), which will be performed according to a standardized protocol (Additional file 2). Patients will perform three sets for each exercise. During the first 2 weeks, the exercises will be performed with approximately 15 repetitions (reps) and an intensity of 15 repetition maximum (RM), and thereafter 2 weeks of 12 reps with 12 RM, and for the remaining 8 weeks 10 reps with 10 RM [28]. The physiotherapist will log the load, repetitions, and pain for each set during the session and progress the load on a set-to-set basis. The patient is instructed to take as many repetitions as possible in each set; if the number of repetitions varies by more than 3 in relation to the number planned, then the load will be adjusted. Both concentric and eccentric phases are performed slowly and in a controlled manner (see Additional file 2 for exercise log).

The engaged physiotherapists in the municipalities are experienced and have been involved in the process of designing/describing the physiotherapy intervention. Prior to initiating the trial, the primary author visited the sites to ensure consistency across the nine rehabilitation centers.

#### General trial treatment procedures

Patients included in the trial will be treated according to the department’s standard procedures for surgery, anesthesia, and perioperative care. Type of operation is determined by a well-defined algorithm based on the type of fracture [32]. Standard perioperative care includes D vitamin and calcium supplementation dependent on the patient’s individual level. Further, a standardized liberal transfusion protocol is used with transfusion if hemoglobin (Hb) is < 9.7 g/dl.

After enrollment, patients will be assessed in regard to the study’s primary and secondary outcomes. Thereafter patients are randomized, and the first injection of the trial solution is administered by the dedicated nurse. In case of the primary nurse being absent, a second nurse trained in the protocol will substitute for her.

After discharge, the patient will receive weekly telephone calls from the project coordinator in order to ensure and monitor compliance. The patient will be asked about the amount of consumed nutritional supplement and attendance at physiotherapy sessions. Further, the patient will be asked about their well-being in order to detect potential side effects of the intervention. An interview guide will be used to assure systematic collection of information.

Every 3 weeks, the patient will attend a control visit at the hospital. The dedicated nurse will carry out blood tests and inject the treatment solution according to randomization group. Compliance with the trial as well as outcome/safety parameters will be monitored. Further, the nutritional supplement covering the following 3 weeks will be handed out at the visit.

The intervention period for the nutritional supplementation and exercise intervention is 12 weeks. The patient will receive the last injection at week 12. Further, at the 12-week appointment, an activity monitor will be applied to the patient’s thigh (activPAL; PAL Technologies, Glasgow, UK), which will monitor activity the following week.

Follow-up will occur during week 14, when patients will be assessed according to the primary and secondary outcomes. To ensure that all potential side effects are detected, one last telephone call is conducted during week 16, and thereafter the patient will have no further obligations in relation to the trial. See Fig. 1 for the flow of enrollment and trial-related events.

### Criteria for discontinuation

Safety parameters are listed under the “Secondary outcomes” heading and will be observed throughout the study. If values of hematocrit, liver tests, and prostate-specific antigen (PSA) exceed the safety thresholds, the treatment with Deca-Durabolin will be discontinued. Further, if women experience androgenic side effects, treatment will be discontinued. Regarding the remaining safety parameters, where no safety threshold is specified, values outside the reference interval will be evaluated by the medical doctors trained in the protocol and relevant action will be taken if necessary.

In accordance with the Declaration of Helsinki, patients have the right to withdraw from the trial at any time for any reason. Further, the investigator has the right to withdraw a patient from the trial at any time if a withdrawal is considered in the best interest of the patient.

Patients who have ceased intervention prior to its determination will be asked to follow the scheduled controls, and data will be collected according to the protocol. Patients who choose to withdraw from the trial will be asked the reason why. However, it is emphasized that the patient is not obliged to state the cause. If a patient drops out and is unwilling to follow the protocol, permission will be asked to continue weekly phone calls to monitor potential side effects (for 4 weeks after last injection). Further, the patient will follow standard treatment for hip fracture and see the orthopedic surgeon at the regular postoperative visit.

### Outcome

Outcomes will be assessed blinded at baseline and at 14 weeks after entering the trial. Safety parameters will be assessed at baseline and 3, 6, 9, 12, and 14 weeks after inclusion. Outcome assessment is carried out primarily by the project coordinator, who is an educated physiotherapist with 13 years of practical experience in orthopedics. In the project coordinator’s absence, an experienced physiotherapist trained in the protocol will conduct the assessments. In the text below, outcome parameters and time of assessment are specified, which are illustrated in Fig. 2.

**Fig. 2 Fig2:**
[figure not shown]
Schedule for enrollment, intervention, and outcome assessments (SPIRIT)

The baseline assessment might extend over 2 days in order to avoid patient exhaustion, and it will be conducted during the time period from postoperative day 3 until postoperative day 10. The follow-up assessment is conducted during week 14 from time of randomization (± 7 days from time of randomization). The control every 3 weeks is conducted within 3, 6, 9, and 12 weeks (± 7 days from time of randomization).

#### Primary outcome

Change in maximal isometric knee-extension strength (N∙m/kg) in the fractured limb (maximal voluntary torque per kilogram body mass) from baseline to the 14-week follow-up. Knee-extensor strength is chosen as the primary outcome because it is closely related to the exposure (strength training), which is what we want in this pilot trial. Hence, we consider the outcome a surrogate outcome measure for a more clinically meaningful one, such as mobility. Pertaining to this, knee-extensor strength is associated with impaired mobility [4, 33].Knee-extensor strength is measured using a belt-fixed handheld dynamometer (Commander Muscle Tester; JTECH Medical, Midvale, UT, USA) [3, 27, 28]. The test is conducted as described by Kronborg et al. [3] with the patient seated on the bedside, with hips and knee joint angle in 90-degree flexion and hands placed on the mattress for support. The lever arm length is measured by tape measure between the lateral epicondyle of the femur and the center of the dynamometer transducer pad placed 4 cm above the lateral malleolus of the tibial bone. Four trials must be completed, and the highest obtained value in Newtons (N) will be used for analysis. Tests are performed with standardized verbal encouragement. The isometric knee-extension strength is expressed in N∙m/kg, which is derived from the units of force measured in Newtons (N) multiplied by the corresponding lever arm measured in meters (m), divided by the weight of the patient in kilograms (kg).

#### Secondary outcomes

The following outcomes will be compared between the two groups. Unless stated otherwise, the change in values are measured from baseline until 14 weeks. Figure 2 illustrates time points for assessment of each outcome.
Maximal isometric knee-extension strength (N∙m/kg) in the fractured limb as a percentage of the nonfractured limb. Description of the measurement method is provided under the “Primary outcome” heading.Maximal isometric knee-extension strength (N∙m/kg) in the nonfractured limb. Description of the measurement method is provided under the “Primary outcome” heading.Hand-grip strength in the dominant hand measured using a digital handheld dynamometer (Saehan Grip, DHD-1; Saehan, Changwon, Korea). Hand-grip strength will be expressed in kilograms. A standardized test protocol will be used similar to the one described by Bodilsen et al. [34].Fat mass (total body weight) assessed by dual x-ray absorptiometry (DEXA), expressed in kilograms. DEXA is performed as a whole-body scan and is conducted in accordance with the department’s standard procedures.Bone mineral density (BMD) assessed by DEXA. Registration of total body, total hip, femoral neck, and lumbar spine BMD. Expressed in g/cm^2^. Further T-score is registered. The scan is performed as a whole-body scan and is conducted in accordance with the department’s standard procedures.Lean body mass assessed by DEXA and expressed in kilograms. Registration of total body, legs bilaterally, and arms bilaterally. The scan is performed as a whole-body scan and is conducted in accordance with the department’s standard procedures.Nutritional screening using the Mini Nutritional Assessment–Short Form (MNA-SF). Total score from 0 to 14 points, high scores indicating better nutritional status. The score is frequently used for assessing nutritional status in patients with hip fracture and predicts mortality and readmissions [35, 36].Gait speed is assessed using the 10-m fast speed walking test, standing start. A standardized test protocol is used, and the best result of three trials is reported in meters walked per second (m/s) [28].The Timed Up & Go Test is performed using a four-wheeled rollator and measured in seconds. The patient has to rise from a chair, walk 3 m, turn around, walk back, and sit down [37]. A standardized instruction will be used [38].The de Morton Mobility Index is used for measuring mobility and consists of 15 mobility items ranging from mobility in bed to dynamic balance. The test result is a total score from 0 to 100, with 100 representing the highest level of mobility [39–41].Activity: Sedentary time (lying/sitting), upright time (standing/walking), steps, and transfers is measured using a body-worn accelerometer-based activity monitor (activPAL) [42]. The monitor will be attached to the thigh. The patient will wear the monitor for 1 week from the time point of the 12-week control.Functional level is assessed by the modified New Mobility Score [43–45]. The patients are interviewed about walking ability indoors, outdoors, and when shopping. At baseline, the score refers to the week prior to hospital admission. The total score ranges from 0 to 9. A higher score indicates greater independence.EQ-5D-3L is used for assessing health-related quality of life [46–48] and is administered via interview. At baseline assessment, the score refers to the time prior to the fracture.Hip fracture-related pain at rest and during outcome assessment is evaluated using the Verbal Rating Scale [49]. The patient is asked to rate the intensity of pain in relation to five adjectives: “no pain,” “slight pain,” “moderate pain,” “severe pain,” and “unbearable pain.” The answer is converted to a number between 0 and 4 on an ordinal scale.A global rating of change scale will be used for assessment of patient-perceived change in walking ability during the trial period. Patients will be asked one question related to change in mobility and have five response options ranging from much better to much worse.The Short Falls Efficacy Scale–International is used to measure the patient’s fear of falling (score range from 7 to 28, with higher scores indicating a greater fear of falling) [50, 51]. It is administered as an interview.Fatigue is assessed using the SF-36 (36-item Short Form Health Survey) vitality subscale, consisting of four items related to fatigue/energy [52, 53]. Scores range from 0 to 100 points; high score defines a more favorable health state. Administered as an interview. The baseline assessment refers to the time prior to the fracture.Depression is assessed using the Geriatric Depression Scale, which is administered as an interview [54, 55]. Score range, 0–15. Baseline assessment refers to the time prior to the fracture.Readmissions within 14 weeks will be assessed through the medical journal.Residential status, including home care, will be recorded by interview or medical journal.Mortality will be assessed through the medical journal/Danish civil register.

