
#### Blood tests

All blood tests are conducted in accordance with the department’s standard procedures.
Total testosterone (nmol/L), luteinizing hormone (IU/L), follicle-stimulating hormone, (IU/L), and sex hormone-binding globulin (nmol/L).Lipid profile (total cholesterol, high-density lipoprotein cholesterol, low-density lipoprotein cholesterol, triglyceride) (mmol/L).C-reactive protein (mg/L).

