It should be noted that the following conditions are considered to occur often after hip fracture surgery and can lead to prolonged hospitalization: nausea, vomiting, dizziness, postoperative urine retention due to catheterization, pain or irritation in relation to the bladder due to catheterization, diarrhea, pneumonia and cardiopulmonary influence, hemoglobin (Hb) < 9.7 g/dl and consequently blood transfusion, and divergent blood tests due to surgery. These will not be registered as AEs during hospital admission. Expected pain from the operation site will not be registered as an AE during the trial period. Further, edema of the fractured limb is common in the postoperative period, and especially for patients with trochanteric fractures compared with those with cervical femoral fractures [4], and will not be reported as an AE. Laboratory test results beyond the reference interval will be recorded as an AE only if they cause a clinical action.

All AEs/ARs will be followed until stabilization by either the relevant hospital department or the patient’s general practitioner.

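### CRP is compared as a raw, unadjusted change from a baseline drawn 3–10 days after surgery, which is likely to cost that one secondary outcome much of its precision

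*Protocol article*

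**What the plan says.** The Secondary outcomes section of the protocol article states that the listed outcomes will be compared between the groups and sets a default: "Unless stated otherwise, the change in values are measured from baseline until 14 weeks". The Blood tests section follows and lists "Total testosterone (nmol/L), luteinizing hormone (IU/L), follicle-stimulating hormone, (IU/L), and sex hormone-binding globulin (nmol/L"), a lipid profile and "C-reactive protein (mg/L"). It gives units only and no other outcome definition.

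That the default reaches these later sub-headings is supported by Criteria for discontinuation, which treats a sub-heading further down as belonging to the same block: "Safety parameters are listed under the “Secondary outcomes” heading and will be observed throughout the study".

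On timing, the Outcome section says of the baseline assessment that "it will be conducted during the time period from postoperative day 3 until postoperative day 10". The Intervention section fixes the order: "After inclusion in the trial, baseline assessments will be performed, and hereafter patients will be randomized (1:1").

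The Data monitoring section lists "divergent blood tests due to surgery" among conditions that often occur after hip fracture surgery and are not recorded as adverse events during the admission. It names no analyte and no size.

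The Statistical analyses section gives a two-sample t test or Wilcoxon rank-sum test for continuous secondary outcomes and mentions no baseline covariate. Safety parameters are to be analysed descriptively.

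**The concern.** A change score subtracts the baseline value in full. That helps when baseline predicts follow-up well and both have similar spread. It hurts when baseline carries a large, transient disturbance that has gone by follow-up. CRP a few days after hip surgery is a likely example: its level would depend on the size of the surgical response and on which day between 3 and 10 the blood was taken. Randomisation is stratified by fracture type and sex, not by sampling day.

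Two things are at stake. The comparison between arms could be so noisy that even a substantial drug effect on week-14 CRP would not show. And a reported mean fall in CRP within an arm would mainly describe recovery from surgery. The article handles a similar problem elsewhere: PSA was moved to the 3-week control because of possible false elevation during admission, and several interview scores refer back to the time before the fracture. CRP has no such provision.

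**Working it through.** **Inputs from the documents.** Change from baseline to week 14, t or Wilcoxon test, no covariate stated, baseline on days 3–10 and before randomisation, 20 completers per group. The only sample-size figure concerns the primary outcome, and it reproduces: Lehr's formula gives 16/(0.2/0.22)² = 19.36, rounded up to 20 per group. It does not bear on CRP except to supply the group size.

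**Inputs that are assumed.** The documents give no CRP level, spread or correlation. Let k be the baseline SD divided by the week-14 SD, and r the baseline to week-14 correlation. Set the week-14 SD to 1.

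**Formulas.**
- Variance of the change: k² + 1 − 2rk.
- Share of that variance explained by baseline: (k − r)²/(k² + 1 − 2rk).
- Variance of the change relative to a baseline-adjusted analysis: (k² + 1 − 2rk)/(1 − r²) = 1 + (k − r)²/(1 − r²). This is never below 1, so apart from one degree of freedom adjustment cannot lose precision.
- Power: take an effect with 80% power on the week-14 value alone at 20 per arm, that is (1.96 + 0.84) × √(2/20) = 0.89 SD. Power on the change is then Φ(2.80/√(k² + 1 − 2rk) − 1.96).

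**Example, k = 1.5 and r = 0.2.** Variance of change = 2.25 + 1 − 0.6 = 2.65. Share from baseline = 1.3²/2.65 = 64%. Ratio to adjusted analysis = 2.65/0.96 = 2.76, so 1/2.76 = 36% of the precision is kept. Power = Φ(2.80/1.63 − 1.96) = 41%.

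| k (r = 0.2) | Share from baseline | Variance ratio, change to adjusted | Power, change | Power, adjusted |
|---|---|---|---|---|
| 1 | 40% | 1.67 | 60% | 82% |
| 1.5 | 64% | 2.76 | 41% | 82% |
| 2 | 77% | 4.38 | 28% | 82% |
| 3 | 89% | 9.17 | 16% | 82% |
| 5 | 96% | 25.0 | 8% | 82% |

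For r from 0 to 0.4 the share is 30–50% at k = 1, 59–69% at k = 1.5 and 75–80% at k = 2. Baseline therefore explains more than half of the variance from about k = 1.5 upward, but not at k = 1.

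**Simulation on a skewed scale.** Lognormal values, 20 per arm, assumed median 80 or 20 mg/L at baseline and 4 mg/L at week 14, log-scale SD 0.7 and 0.9, correlation 0.2 on the log scale. With no effect, the t and Wilcoxon tests on change reject in 4–5% of runs, so type I error is held. With week-14 CRP halved, they reject in 5–10%, against about 64% for Wilcoxon on the week-14 value and about 67% for the log week-14 value adjusted for log baseline.

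**Scale or change rule?** Over a wider range of assumed CRP values, again with week-14 CRP halved, power was about 5–20% for the raw change, 50–67% for the change on the log scale, 64–74% for Wilcoxon on the week-14 value and 65–76% for the adjusted log analysis. Taking logs recovers much of the loss. So does dropping the subtraction without any log, which shows that the raw change rule is itself costly.

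**Stable analytes.** With k = 1, the change has variance 2(1 − r), the unadjusted week-14 value 1, and the adjusted value 1 − r². At r = 0.8, for illustration, these are 0.40, 1 and 0.36. Once r exceeds 0.5, an unadjusted week-14 value is worse than the change; the adjusted analysis is no worse than either.

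**The case against.** The strongest reply is that the documents do not establish any size. They contain no CRP level or spread, and at k = 1 baseline explains only 40% of the change variance (r = 0.2). That stands: the size is conditional on an assumed spread.

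Second, much of the power gap comes from analysing a skewed marker on its raw scale, and a transformation or covariate may be specified in an analysis plan that is not shown. That is partly right. But the article does state the outcome as a change and does state the tests, and the week-14 value recovers the power without a log. The article also says "Figure 2 illustrates time points for assessment of each outcome", and that figure is not available here; from its description it schedules assessments, whereas the change rule is in the text.

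Third, the repair does not make CRP well powered. For a 25% reduction even the adjusted log analysis has under 20% power at this size, and the article says that the pilot only explores potential effect and is not sufficiently powered. That stands too. The case rests on using the same samples better, not on rescuing a test.

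A reader might infer that hormones and lipids are equally compromised. The documents do not support this: the only basis is one generic phrase in an adverse-event recording rule, which names none of them. A blanket switch to unadjusted week-14 values could reduce their precision, particularly in a trial that enrols both sexes.

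**Conclusion.** The point holds for CRP, as a minor one. The stated analysis compares a raw change from a postoperative baseline, without adjustment, at a time when the article expects blood values to be disturbed by surgery. If the postoperative SD is at least about 1.5 times the week-14 SD, baseline explains more than half of the change variance for every correlation tried (0 to 0.4). At a correlation of 0.2, at most about 36% of the available precision is kept. This rests on an assumed spread that is plausible for CRP but not documented.

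A reader might go further and infer that the comparison between arms is biased. It is not: baseline precedes randomisation in both arms, so the surgical response adds noise only, and simulated type I error was 4–5%. Nor does the point reach the primary outcome, the sample size or the safety blood tests, which are descriptive.

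**What to change.** For CRP, compare log week-14 values between arms with log baseline as a covariate, and report the ratio between arms with a 95% CI. Give change from baseline as description only, with a note that it includes recovery from surgery.

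For hormones and lipids, do not switch to the unadjusted week-14 value. If their analysis is changed at all, compare week-14 values with the baseline value as a covariate.

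The cost is a sentence or two in the analysis plan, fixed before the allocation is revealed. The same samples, visits and patients are used.

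Suggested wording: *CRP will be compared between arms at week 14 on the log scale by linear regression with log baseline CRP as a covariate; the ratio of geometric means will be reported with its 95% CI. Change from baseline will be presented descriptively.*
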